## Abstract

**Background:**

The NHS Talking Therapies for Anxiety and Depression programme (‘TTad’; formerly Improving Access to Psychological Therapies ‘IAPT’) delivers high-intensity cognitive behavioural therapy (CBT) to over 200,000 individuals each year for common mental health problems like depression and anxiety. More than half of these individuals experience comorbid personality difficulties, who show poorer treatment outcomes. TTad therapists report feeling unskilled to work with clients with personality difficulties, and enhancing the training of TTad therapists may lead to improved treatment outcomes for individuals presenting with secondary personality difficulties alongside depression and anxiety.

**Methods:**

This is a pre-post non-randomised mixed-method feasibility study, exploring the feasibility and acceptability of a 1-day training workshop for high-intensity (HI) CBT therapists. The workshop is focused on understanding and assessing personality difficulties and adapting HICBT treatments for anxiety and depression to accommodate client needs. The feasibility and acceptability of the workshop and the evaluation procedures will be investigated. It will be examined to what extent the workshop provision leads to improvements in therapist skills and confidence and explored to what extent the training has the potential to enhance clinical outcomes for this client group.

**Discussion:**

This feasibility study will provide data on the acceptability and feasibility of delivering brief therapist training to adapt usual HICBT to optimise care for individuals with secondary personality difficulties seeking treatment in TTad services for a primary problem of depression and/or anxiety. The study will also evaluate proof of concept that such an approach has the potential to improve clinical outcomes for those with secondary personality difficulties and report any possible harms identified. The study will inform the design of a future randomised controlled trial designed to test the effectiveness and cost-effectiveness of the training.

**Trial registration:**

ISRCTN81104604. Submitted on 6th June 2022. Registration date: 3rd January 2023.

**Supplementary Information:**

The online version contains supplementary material available at 10.1186/s40814-023-01394-z.

## Background

NHS Talking Therapy for Anxiety and Depression (TTad) provides access to evidence-based psychological therapies for common mental health problems (predominantly anxiety and depression) in primary care across the English National Health Service (NHS). Formerly known as Improving Access to Psychological Therapy (IAPT) services, in 2021, these services received 1.81 million referrals for talking therapies, with over 660,000 going on to complete a course of treatment [1]. TTad services span Steps 2 or ‘low-intensity (LI)’ and 3 or ‘high-intensity (HI) treatments of the stepped-care model of mental health service delivery) [2]. In 2021, the most commonly delivered treatment was a HI cognitive behavioural therapy (CBT)—accounting for 46% of courses, followed by a LI format—book-assisted guided self-help (26.4%) [1].

Many individuals accessing TTad treatments experience clinically significant improvement (66.9% reliably improved in 2020–2021) and move into recovery (50.2% recovered in 2020–2021) [1]. However, this leaves almost a third who do not show clinically significant improvement and almost half of those who are treated who do not recover. One way to improve treatment outcomes is to identify subgroups of individuals who are not currently showing optimal outcomes and to refine the treatment they are offered to better meet their needs. It is increasingly clear that current difficulties managing emotions, relationships, and sense of self (often associated with exposure to early life adversity or trauma) are linked to poorer response to standard TTad treatments for depression and anxiety [3–5]. These presenting issues are sometimes referred to as ‘personality difficulties’ or ‘complex emotional difficulties’ and are believed to fall on the milder end of the personality disorder spectrum (see the dimensional personality disorder framework proposed in ICD-11) [6–8]. While not routinely screened for, pilot initiatives have demonstrated that between 69 to 81% of TTad clients present with emotional, interpersonal, and identity difficulties associated with ‘personality difficulties’ [5, 9].

While these individuals with personality difficulties do still benefit from TTad interventions, their rates of clinically significant improvement and recovery are lower than in those individuals without personality difficulties. For example, recovery rates for this group are estimated to be around 40%, below the 50% national target, and the 50.2% observed recovery rate observed across all client groups in 2020–2021 [1, 10]. These effects held over and above intake depression and anxiety severity, other demographic features, and number of treatment sessions attended [4, 5].

A subtly different pattern emerges in reviews of CBT outcomes in the clinical trials literature [11, 12]. While there is evidence that clients with a comorbid personality disorder diagnosis have higher symptom levels at the end of CBT treatments for both anxiety and depression, this effect does not consistently emerge when controlling for intake depression and anxiety symptom severity [11, 12]. These secondary analyses are at risk of type II error as the studies were not powered for subgroup analyses and did not stratify clients to treatment on the basis of personality disorder subgroup status. Nevertheless, current data suggest that therapists delivering CBT under ideal conditions can achieve broadly comparable levels of change in clients with and without a comorbid diagnosis of personality disorder. This suggests therapists in TTad settings may benefit from additional training to optimise their ability to deliver existing CBT treatments in the context of these more complex presentations, rather than there being a need to introduce entirely new treatment protocols.

In qualitative evaluations, TTad clients with personality difficulties describe how care has not always felt tailored to their needs [13] and TTad clinicians report feeling unskilled and lacking in confidence to undertake therapy with this client group, and propose core TTad training should include focused training on this topic [14]. In particular, clients viewed more structured approaches as less acceptable and valued more flexible approaches [13], and therapists were less likely to report difficulties ‘maintaining control’ over sessions if they adopted more flexible approaches [14]. Furthermore, recent updates to clinical guidance on depression now reflect the importance of assessment of interpersonal difficulties and tailoring care to cover these issues where they are acting to maintain depression [15].

Despite increasing awareness and adoption of a dimensional framework, and clinical guidance now stating that individuals with this diagnosis should not be routinely denied access to treatments for depression/anxiety [15], ‘personality disorder’ continues to be poorly understood, stigmatised [16], and be associated with inequitable access to care [17]. Previously, the use of targeted educational interventions like the co-produced Knowledge and Understanding Framework [18] and e-learning packages have been shown to lead to significant shifts in mental health workforce attitudes towards personality disorders and workforce burnout in other health care settings [19–22]. Broader literature also shows mental illness stigma can be significantly improved by interventions that shift categorical to continuum beliefs [23].

In sum, concurrent personality difficulties appear to predict poorer outcomes in TTad services, which may be distinct from outcomes in research settings. Outcomes in the TTad setting may be improved by targeting therapist attitudes and understanding of a dimensional framework of personality difficulties and enhancing their clinical skills to assess these difficulties (including whether they can be appropriately managed in a TTad setting) and tailor depression and anxiety treatments accordingly. One significant opportunity to upskill existing workforces with minimal costs involved is to use existing continuing professional development (CPD) time to deliver focused clinical workshops, which may translate into improved clinical outcomes for clients, as well as potentially increasing therapist job satisfaction and wellbeing. This pragmatic approach to improving clinical outcomes for clients with concurrent personality difficulties in TTad services has not previously been evaluated.

This observational study aims to explore the preliminary feasibility and acceptability of a 1-day workshop focusing on enhancing the knowledge, skills, and confidence of HICBT therapists to assess and make evidence-based adaptations to depression and anxiety treatments for TTad clients with concurrent personality difficulties. The study will also examine if the workshop has any impact on workforce wellbeing and assess preliminary proof of concept that training has the potential to lead to improvements in clinical outcomes for clients with co-morbid personality difficulties accessing HICBT treatments for depression and anxiety treatments.

## Methods/design

### Objectives

The over-arching aim of this study is to evaluate the feasibility and acceptability of the training intervention.

The secondary aims of the research are to (1) establish proof of concept that training leads to positive changes in therapist attitudes towards working with this group and improved confidence in key skills covered in training, (2) evaluate the impact of training on therapist wellbeing and burnout, and (3) evaluate preliminary proof of concept that the training has potential to improve outcomes for individuals with co-morbid personality difficulties.

We will set and evaluate continuation rules to inform continuation to definitive randomised evaluation.

### Design

We will conduct a pre-post non-randomised mixed-methods feasibility study, comparing therapist attitudes and workplace wellbeing from before and after the training workshop. We will also conduct a preliminarily pre-post evaluation of routinely collected service-level clinical outcomes on clients attending for treatment that meet the criteria for personality difficulties.

### Study setting

We will purposefully recruit at least three TTad services, chosen to reflect diversity in terms of urban/rural context, levels of deprivation, and ethnicity. Services willing to screen for personality difficulties as part of routine assessment will be eligible to participate as a research site.

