**Routine clinical outcomes on clients with personality difficulties (measured in 6 m before and after the workshop)**		
** Depression symptoms**	Patient Health Questionnaire (PHQ-9 [44];)—a 9-item self-report measure of frequency of depression symptoms (for example, ‘Little interest or pleasure in doing things’). Respondents are asked to rate frequency of symptoms over the past 2 weeks on a 4-point Likert scale from ‘Not at all’ to ‘Nearly every day’. This scale is validated for use in adolescents and adults.	First and last session
** Anxiety symptoms**	The Generalised Anxiety Disorder scale (GAD-7; [45])—a 7-item measure of anxiety symptom (for example, ‘Feeling nervous, anxious or on edge’) frequency over the past 2 weeks, scored on a 4-point Likert scale from ‘Not at all’ to ‘Nearly every day’.	First and last session
** Work and social functioning**	Work and Social Adjustment Scale (WSAS; [46])—a 5-item measure of impairment in daily functioning (for example, ‘Because of my [problem] me ability to work is impaired’) rated on a 9-point Likert scale from ‘Not at all’ to ‘Very severely’.	First and last session
** Measure of personality difficulties**	Standardised Assessment of Personality: Abbreviated Scale—Self Report version (SAPAS-SR; [47, 48])—8-item binary response (yes/no) measure of personality difficulties (for example, ‘In general, do you have difficulty making and keeping friends. This scale is adapted for use as a self-report questionnaire and respondents are asked to indicate ‘Yes’ when the experience applies to them ‘most of the time in most situations’. This scale has been widely used for rapid screening for personality difficulties within the TTad setting for research purposes and has been adopted into routine practice in some services [4, 5, 9].	First session /instance
** Qualitative experiences of treatment**	Patient Experience Questionnaires	Treatment end

**Table 2 Tab2:** Feasibility and acceptability data, method of measurement, and continuation rule to proceed to randomised evaluation without modification

Feasibility/acceptability outcome	Measurement	Continuation rule
**Recruitment**	*Quantitative data*	
	Number of TTad sites recruited to the research project	≥ 3 IAPT sites recruited
	Percentage of eligible therapists attending the training at each site	≥ 60% attendance
	Percentage of attending therapists completing pre- and post-training surveys	≥ 80% data availability

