	Percentage of attending therapists completing 3-month follow-up surveys	≥ 60% data availability
**Acceptability**	*Quantitative data*	
	Feedback data on training (that that the training was theoretically interesting, clinically useful, well presented, and would recommend to other HICBT therapists)	60% agree or strongly agree with each item
	*Qualitative data*	
	Written feedback from therapists on the value of training	No significant concerns emerge about training that cannot be resolved
	Qualitative interviews with therapists	No significant concerns emerge about training that cannot be resolved
	Reporting/identification of serious concerns about the acceptability and feasibility of training by key stakeholders	No serious concerns emerge about training that cannot be resolved
	Reporting/identification of serious negative consequences for therapist participants or the clients they subsequently work with as a result of the training (unexpected, clearly research- or training intervention-related serious adverse reactions).	No serious consequences raised
**Clinical outcome data completion**	*Quantitative data*	
	Percentage of TTad clients receiving routine care during the study with sufficient data for inclusion in secondary analyses (at least one measure of SAPAS-SR personality difficulties and at least × 2 measures of the TTad service minimum dataset [PHQ-9, GAD-7 and WSAS])	≥ 60% data availability
**Proof-of-concept**	*Quantitative data*	
	Therapist attitudinal change in confidence to recognise, assess and triage clients with personality difficulties; to adapt key skills for working therapeutically with this group; and in positivity towards working with this group after completing the training in each service.	Significant improvement from pre to post in all 5 attitudinal domains

In addition to these measures, we will capture clinical data to enable us to generate metrics of engagement including discharge code and number of sessions marked ‘Attended’, ‘Did Not Attend’, and ‘Patient Cancelled’. In line with standard reporting of TTad outcomes, we will also compute the following metrics from clinical outcomes: (i) ‘Recovery’—as defined by moving ≥ 10 to ≤ 9 on the PHQ-9 and from ≥ 8 to ≤ 7 on the GAD-7; (ii) ‘Reliable Improvement’—as defined by improving by ≥ 6 points on the PHQ-9 or ≥ 4 points on the GAD-7; and (iii) ‘Reliable Recovery’—as defined by fulfilling criteria for both ‘recovery’ and ‘reliable improvement’ [49].

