#### Clinical outcomes

We will report descriptive statistics (means, standard deviations) to describe the clinical measures and client characteristics at intake within the pre- and post-training intervention cohorts (those engaging in treatment in the 6 months pre- compared to 6 months post-therapist training). This will include PHQ-9, GAD-7, and WSAS mean scores; the proportion of clients showing mild, moderate, and severe cut-offs on each scale; and the proportion of clients scoring 3 or more on the SAPAS-SR (indicative of personality difficulties).

This research is a multi-site observational study prior to conducting a definitive evaluation with a randomised trial and therefore has not been a priori powered to inferentially examine between cohort differences in clinical outcomes. However, it is both possible and useful to estimate the between-cohort effect size (and their 95% confidence interval) on client outcomes to help inform decisions to continue to a definitive evaluation of the training intervention and to inform future power calculations. We will therefore report the observed effect sizes but not *p* values. These analyses will focus solely on the subgroup of participants meeting the criteria for probable personality disorder (3 or more on the SAPAS-SR), which we estimate from previous research to be between 69 and 81% of client treatments [5, 9]. A series of linear regressions will examine whether treatment-cohort (treated before or after training) predicts the number of treatment sessions attended and post-treatment levels of depression (PHQ-9), anxiety (GAD-7), and functioning (WSAS). All analyses will include the training site as a covariate. The post-treatment analyses will adjust for the pre-treatment level of the relevant variable. Comparable binary logistic regressions will examine binary outcomes (rates of reliable improvement, recovery, and reliable recovery; rates of clients with planned discharges), again seeing if the treatment cohort (before or after training) predicts each variable and covarying for the training site. As we do not anticipate sufficient statistical power to do inferential statistics, we will examine the distribution of effect sizes, potentially using confidence intervals and Bayesian methods relative to estimates of minimum clinically important difference on clinical outcomes (cf., [55–58]). All quantitative analyses will take place in SPSS or R.

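### The before-training cohort may be incompletely screened with SAPAS-SR, and a 60% availability rule with no cohort split can pass when it is

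*Protocol article*

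**What the plan says.** Study setting gives the only screening condition for a site: "Services willing to screen for personality difficulties as part of routine assessment will be eligible to participate as a research site". The article does not treat such screening as universal. Background introduces its prevalence range with "While not routinely screened for, pilot initiatives have demonstrated that between 69 to 81% of TTad clients", and Table 1 says of SAPAS-SR that it "has been adopted into routine practice in some services".

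The Clinical outcomes section defines the cohorts as "those engaging in treatment in the 6 months pre- compared to 6 months post-therapist training" and restricts the between-cohort analyses: "These analyses will focus solely on the subgroup of participants meeting the criteria for probable personality disorder", meaning a SAPAS-SR score of 3 or more. The outcomes are sessions attended, post-treatment PHQ-9, GAD-7 and WSAS, reliable improvement, recovery, reliable recovery and planned discharge. Site is a covariate throughout.

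Table 1 gives the SAPAS-SR time point as "First session /instance". In Table 2 the clinical data rule is the "Percentage of TTad clients receiving routine care during the study with sufficient data for inclusion in secondary analyses", with a threshold of 60%. A client counts with one SAPAS-SR, whenever it was taken, plus at least two sets of the routine measures. The rule names no cohort or site, and Primary analyses plans a single number and percentage. Elsewhere in Table 2 the split is explicit: attendance is judged per site and attitude change per service.

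**The concern.** A client without a SAPAS-SR cannot be placed in the analysis subgroup. If a service begins screening because it joins the study, clients seen before that date either have no score or have one only if they were still attending when screening began. After training, screening would be in place from intake. The two cohorts would then be assembled by different routes.

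Two things are at stake. First, the continuation rule is meant to show whether the clinical data can support the planned analysis, and it could be met although one side of the comparison is mostly missing. Second, entry through late screening depends on retention, and sessions attended and planned discharge are themselves outcomes. Part of any before/after difference could then reflect how clients came to be screened. The resulting effect sizes are intended to inform both the decision to continue and the sample size of the later trial.

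**Working it through.** **Inputs.** From Service-level secondary data sample: 3 sites, 40 therapists per site, 20 clients per therapist per 6-month period. From Table 2: 60% threshold. From Background: recovery of about 40% in this client group. The completeness values below are assumptions, since the article gives none. Completeness means meeting the whole Table 2 definition.

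**The article's own figure.** 3 × 40 × 20 = 2,400 per period, and 2 × 2,400 = 4,800. This reproduces the stated total.

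**What the rule allows.** With equal cohorts, overall completeness = (before + after)/2. Meeting 60% needs 0.60 × 4,800 = 2,880 complete clients, so the lowest passing before completeness is 1.20 − after completeness.

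| After cohort | Lowest before cohort that passes | Before clients |
|---|---|---|
| 100% | 20% | 2,880 − 2,400 = 480 |
| 90% | 30% | 2,880 − 2,160 = 720 |
| 80% | 40% | 2,880 − 1,920 = 960 |

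A 60% rule applied to each cohort would need 0.60 × 2,400 = 1,440 in each.

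**No before screening anywhere.** The maximum is (0 + 100%)/2 = 50%. The rule fails and the problem shows.

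**Some sites without before screening** (equal sites, the same completeness c wherever screening operates; k sites lacking it; before = c(3 − k)/3, overall = c(6 − k)/6):

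- k = 1, c = 90%: before 60%, overall 75%, passes.
- k = 1, c = 80%: before 53%, overall 67%, passes.
- k = 2, c = 90%: before 30%, overall 60%, just passes.
- k = 2, c = 80%: before 27%, overall 53%, fails.

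**Screening starts m months before training at every site** (clients start evenly over the window and are screened only at the first session; before = c × m/6):

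- m = 3, c = 90%: before 45%, overall 67.5%, passes.
- m = 2, c = 90%: before 30%, overall 60%, just passes.
- m = 2, c = 85%: before 28%, overall 57%, fails.
- m = 1, c = 90%: before 15%, overall 52.5%, fails.

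Clients screened late would add to the before count, so they make the rule easier to meet.

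**Size of a possible bias.** Assume no training effect, true recovery of 40%, 75% of clients scoring 3 or more, about 30% complete before and 90% after. Let a and b be the chance that a recovered and a non-recovered before client has a SAPAS-SR. Apparent before recovery = 0.4a/(0.4a + 0.6b).

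- a = b = 30%: apparent recovery 40%, difference 0.
- a = 35%, b = 27%: 0.140/0.302 = 46%; after minus before is −6 points (95% CI −11 to −2).
- a = 27%, b = 32%: 0.108/0.300 = 36%; after minus before is +4 points (95% CI −1 to +9).

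Bias needs a link between being screened and outcome, and its sign depends on that link.

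**The case against.** The strongest reply is that the article plans for SAPAS-SR in both periods. Table 1 places it in a block covering the 6 months before and after the workshop, the sample size section expects the same 69 to 81% to qualify in each cohort, and Clinical outcomes describes the share scoring 3 or more within each cohort. Willingness to screen is an eligibility phrase and not a start date, and the full protocol, not shown here, may set a screening lead-in. This stands as a reason not to say that before data will be missing. It does not close the gap: nothing in the article makes earlier screening a condition, and it says that screening is not universal.

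Three stronger readings do not hold. A reader might infer that the 60% rule would miss a complete absence of before screening; with equal cohorts it would not, because availability cannot exceed 50%. A reader might infer that the comparison is biased; the documents show only a route by which it could be. A reader might expect a site with no before data to distort the contrast; because site is a covariate, such a site adds almost nothing to it and mainly costs precision.

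It is also fair that the comparison is exploratory, reports no p values, and has no continuation rule tied to its result. Intake descriptives by cohort might expose an imbalance, though no threshold acts on them. That the rule is a single overall percentage is inferred from the absence of any split, but the explicit splits elsewhere in Table 2 make it the natural reading.

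**Conclusion.** The point holds in a limited form. As written, the article allows the before cohort to be partly unscreened or screened mid-treatment, and its availability rule can be met with before-cohort completeness of 20 to 40% when after-cohort completeness is 100 to 80%. What can go undetected is partial or site-specific absence.

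The figures assume equal cohorts, as the article projects. If the before cohort were smaller, even total absence could pass: with 90% completeness after training, this happens once before clients are no more than 1 − 0.60/0.90 = 33% of the total.

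Bias is conditional. It arises if screening begins partway through the before window and having a SAPAS-SR is related to outcome. The site covariate does not remove selection within a site. The illustrations of −6 and +4 points show that its direction is unknown; they are not estimates for this study. The matter deserves a change despite the exploratory status, because it alters what a stated continuation rule can conclude and because the effect sizes are meant to feed the next trial.

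**What to change.** In Table 2 and Primary analyses, apply and report the 60% rule separately for the before and after cohorts at each site. On the article's projection each such cell holds 40 × 20 = 800 clients, so 480 would be needed.

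In Clinical outcomes, restrict the comparison, or at least a stated sensitivity analysis, to clients whose SAPAS-SR was recorded at or before the first treatment session, and use only before-window time when routine screening was in place at that site. A site with no such time would contribute to the therapist outcomes but not to the clinical contrast.

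The change needs revised wording and the SAPAS-SR date in the data extract. The price is fewer before clients, and so wider intervals, at sites that started screening recently.
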